### Methods against bias

We take the following action to minimize potentials for biased results. Assessments will be conducted by trained interviewers unaware of the study condition, at home and individually in separate rooms for participating family members to ensure privacy and confidentiality and to reduce drop-out. Blinding of families and intervention facilitators is not possible. To maintain program retention, during the family sessions we offer child care for families who have younger siblings they cannot leave at home alone [69]. Moreover, participating families will be financially rewarded for complete program retention and for each completed follow-up data collection. To avoid crossover in the intervention groups, we aim for implementation of parallel group training with regard to both intervention conditions.

Data management will be performed locally following the guidelines of Good Clinical Practice (GCP) and will be monitored (including source data verification), collected, and preprocessed by the Clinical Trial Center North, thus an external clinical research organization (CRO).

A Data and Safety Monitoring Board (DSMB) will be implemented once the recruitment has started with regular meetings (preferably by telephone conferences), with an open and closed part with and without the coordinating investigator. The DSMB will monitor study and recruitment progress, protocol deviations, loss-to-follow-up data, serious adverse events (SAE) and adverse events (AE), and all problems of the study and decide independently from the coordinating investigator whether the study can be continued or a recommendation is given to change the design or stop the trial. The members of the DSMB will be experienced scientists who are not otherwise involved in the study, independent of the investigators and the trial sponsor, and will have no conflict of interests.

Recruitment centers and all researchers conducting the consenting process and baseline assessments will be repetitively trained to conceal any information which could lead the participants to associate an intervention timing with an intervention arm in order to improve allocation concealment.

The Institute of Medical Biometry and Epidemiology at the University Medical Center Hamburg–Eppendorf supports the trial in terms of database development, randomization, data management, and analyses (including for plausibility check and analysis of the missing data structure). It will also provide the DSMB with safety reports and methodological expertise if required.

Prepublication of the trial design and trial registration in a public database before recruitment has started, and adherence to the CONSORT statement for randomized controlled trials will further minimize potentials for bias. Data collection and entry will be conducted according to standardized protocols. Self-report data will be collected mainly using digital methods, thus minimizing errors of data entry. Any data collection using paper–pencil measures (e.g., assessment of safety endpoints) will be computerized by trained staff using the EpiData software, with double entry and range checks for data values. All data will be stored securely and in line with current guidelines and regulations concerning data safety and confidentiality of the study participants.

Trial results will be reported at international conferences and meetings and published in open access and peer-review journals to ensure a maximized and high-quality dissemination of the study findings.

### Trial governance

The study is part of the national study group “IMAC-Mind” (Improving Mental Health and Reducing Addiction in Childhood and Adolescence through Mindfulness: Mechanisms, Prevention and Treatment), which focuses on the clinical utility of mindfulness-oriented approaches to prevention and treatment of SUD in different developing populations, from the prenatal period throughout the second decade of life. The consortium comprises eight subprojects with five clinical studies of mindfulness-based approaches to SUD prevention and treatment (see www.imac-mind.de) and is coordinated by the first and the last authors. It is supervised by a project steering committee comprising the principal investigators of all subprojects. The trial is supported by the Institute of Research and Education GmbH associated with the Medical School Hamburg (MSH). It is monitored by an external CRO and overseen by an independent DSMB. The project receives national funding by the German Federal Ministry of Education and Research (Grant: 01GL1745F). The sponsor of the trial described in this protocol is the University Medical Center Hamburg–Eppendorf. The funding source has no role in the design of this study and will not have any role during its execution, analyses, interpretation of the data, or decision to submit results.

### Ethics

We will design, conduct, and evaluate the trial following the rules of GCP and commit ourselves to the Declaration of Helsinki [109]. Names and person-related data will be treated according to the conditions of the German Data Protection Act. Informed consent will be obtained from all participants prior to participation and can be withdrawn at any time.

Although the planned prevention trial targets universal families, it may assemble families with children manifesting behavioral difficulties who may be more willing to apply to participate in the study and/or may be prioritized in practitioner referrals as families in need of support. Risks associated with trial participation may thus include harmful peer modeling effects which may arise from aggregating youth with early indications of mental health problems. Participant information and safety will therefore be ensured by careful monitoring and supervision of intervention delivery personnel, documentation, and stopping and referral rules where appropriate. Beyond this issue, prior research on comparable interventions indicates no harm associated with trial participation.

SAE and AE will be carefully monitored, documented, and reported to the coordinating investigator and the Data and Safety Monitoring Board (DSMB) members within 1 week of the initial observation to determine the benefit–risk of trial continuation and adequate participant support.

The study was granted ethical approval by the responsible Ethics Committees of the Chamber of Physicians Hamburg (PV5932) and the study was registered in the DRKS public database (DRKS00015678). Any changes to this study protocol will be reported to the Ethical Committee for further review and modifications will be subsequently made in the trial registry if necessary.

## Discussion

This trial builds on the emerging evidence for the preventative utility of MT in youth and family settings, and aims to evaluate the effectiveness of a mindfulness-enhanced family-based substance use prevention program targeting both adolescents and their parents to prevent adolescent substance use using randomized controlled methods in a comparably large sample and a substantial follow-up period. Existing studies of MT among young people are largely limited to educational settings, and there are no controlled studies on both parent-directed and adolescent-directed approaches. Moreover, it is unclear whether such MT has preventive effects for substance use outcomes in adolescence.

In this trial, we integrate MT into an established prevention program that has a sound evidence base as a successful program to prevent adolescent substance use and promote positive youth development. Testing MT against an already efficacious program in an active control group design provides a direct estimate of the additive effects of MT over a program that is considered the current best practice for family-based substance use prevention [33]. While MT is usually delivered as a standalone intervention, we will directly test the assumption that an effective program can be improved using MT. By integrating the family as an important socialization context, we aim to contribute to the evidence base of MT approaches outside the educational setting, where youth-directed MT approaches are typically implemented. Finally, while we rely on self-report data for the primary substance use outcome, we include neurobehavioral measures to explore effects of MT on self-regulation skills implicated in addiction development and mental health.

With this trial, we expect to contribute to establishing MT as an effective approach for family-based prevention of substance use and promoting mental health in adolescence and to provide new insights into the mechanisms of action of MT.

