**Methods/design:**

The trial design is a superiority, two-arm, randomized controlled trial in which families will participate either in the full curriculum of the evidence-based Strengthening Families Program 10–14 (SFP 10–14, German adaptation) or in a mindfulness-enhanced version of this program (SFP-Mind). Both seven-session interventions are highly structured and will each be delivered over a period of approximately 7 weeks. The experimental intervention SFP-Mind is a modified version of the SFP 10–14 in which some elements were eliminated or changed to enable the inclusion of additional parent-directed and adolescent-directed mindfulness components. The primary outcome is adolescent self-reported alcohol use based on an alcohol initiation index at 18-month follow-up. Dispositional mindfulness, impulsivity, and emotion regulation will be included as secondary outcomes and potential mechanisms of action. The study will recruit and randomize 216 adolescents, aged 10–14 years, and their parents who will be followed up for 18 months.

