## Methods/design

### Study design

We will apply a superiority, two-arm randomized, prospective, observer-blind controlled trial in which an MT-enhanced family-based prevention program will be compared with the SFP 10–14, a previously established efficacious “standard” program version without MT components. This program has been shown to improve symptoms of psychopathology and to delay uptake of substance use in previous studies [28–30], including a German adaptation trial [34]. Intervention conditions in both trial arms are comparable in the frequency and duration of personal contacts. Although inclusion of an additional no-treatment control group in a three-arm trial appeared a desirable option, we consider a two-arm trial adequate for two reasons: firstly, it is an adequate design to address the primary research question, whether MT adds value over the evidence-based standard program version (for a similar approach, see [59, 60, 65]); and, secondly, recruitment is often limited because program deliverers in the field are reluctant to refer families to RCT studies with non-active or minimal control group designs [66, 67].

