### Intervention fidelity

To ensure both programs are delivered with expertise and fidelity, at least two of the three intervention trainers will be social workers from the field with experience in working with adolescents or families, who have completed the mandatory 3-day certified SFP 10–14 training program. The SFP-Mind facilitators will either be the program developers or facilitators trained by experienced personnel in teaching the novel mindfulness modules and require having personal experience with MT prior to starting the group trainings. This way, we aim for an adequate standard for MT delivery that is comparable to other mostly school-based MT approaches among universal youth populations [43, 71–74] and family-based approaches [65]. While we acknowledge the importance of mindfulness skills among trainers, our approach reflects externally valid conditions which might be found in real-world conditions, thus maximizing generalizability. Scripted manuals in both conditions support clarity, fidelity, and adherence, which will be monitored during the study. Specifically, two independent raters will estimate adherence in videotapes of selected sessions using a list of prescribed activities as applied in a previous study [34] and with modifications made for novel MT program content. Data on acceptability of the programs by the study participants and the facilitators will also be collected.

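### The two-arm contrast estimates the net effect of SFP-Mind as a package, not the additive effect of mindfulness that the article claims, because SFP-Mind also removes or alters standard SFP content

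*Protocol article*

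**What the plan says.** The Abstract (Methods/design) defines the two arms. Controls take part in the "full curriculum of the evidence-based Strengthening Families Program 10–14". The experimental arm receives a modified version in which "some elements were eliminated or changed to enable the inclusion of additional parent-directed and adolescent-directed mindfulness components". The Study design section adds: "Intervention conditions in both trial arms are comparable in the frequency and duration of personal contacts".

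The aim and the interpretation are nevertheless worded as an add-on. Study design gives the primary research question as "whether MT adds value over the evidence-based standard program version", and uses it to justify having two arms. The last paragraph of the Background hypothesises that the addition of mindfulness to SFP 10–14 will make the programme more effective. The Discussion says the active-control design "provides a direct estimate of the additive effects of MT over a program" that counts as current best practice, and continues: "we will directly test the assumption that an effective program can be improved using MT". Neither Study design nor the Discussion mentions that the experimental arm gave up or altered some standard content.

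**The concern.** An additive effect of mindfulness is the difference between standard SFP with mindfulness added and standard SFP without it. The Abstract describes a substitution: some SFP content makes way for mindfulness content. The contrast therefore mixes a possible gain with a possible loss, and the article claims to measure the gain alone.

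What is at stake is how the result is read. A null result could be reported as showing that mindfulness adds nothing, when a benefit may have been offset by the displaced content. A positive result could be reported as the effect of mindfulness, when part of it may come from the changes made to SFP itself.

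**Working it through.** **1. What each arm contains.** Write S for the effect of the full SFP 10–14 curriculum, R for the contribution lost by removing or changing some of its elements, and M for the contribution of the mindfulness components. Effects are taken to add up, for simplicity.

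- Control arm (Abstract): S
- SFP-Mind arm (Abstract): S − R + M
- Contrast the trial estimates: (S − R + M) − S = M − R
- Contrast the Discussion claims: (S + M) − S = M

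The two agree only if R = 0. The trial supplies one contrast for two unknowns, so M and R cannot be separated, whatever the sample size.

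**2. Can R be taken as zero?** The article gives no ground for it. Study design treats SFP 10–14 as an established efficacious programme, and the Background reports that the investigators' own earlier trial found it effective against tobacco use and conduct problems. If the curriculum works, its elements cannot be presumed inert. R could also be negative, if the cut elements were unhelpful or the changes were improvements. The direction of the gap is therefore not known either.

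**3. What each result could mean.**

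- M − R = 0 fits M = R = 0 (mindfulness does nothing), and equally M = R > 0 (mindfulness helps and the lost content cost as much).
- M − R > 0 fits M > 0, and equally M = 0 with R < 0 (the revision of SFP helped, not the mindfulness).

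**4. Does any figure in the plan depend on the additive reading?** The Sample size section gives d = 0.40, correlation r = 0.30, two-sided alpha 5%, power 80%, 91 per arm, and 15% loss.

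- Residual SD factor: √(1 − 0.30²) = 0.954
- Noncentrality at n = 91: (0.40 / 0.954) × √(91/2) = 2.83, with 2 × 91 − 3 = 179 degrees of freedom
- Power from the noncentral t: 0.803 at 91 per arm, 0.799 at 90 per arm. So 91 is reproduced.
- Recruitment: 91 / 0.85 = 107.06, rounded up to 108 per arm, or 216 in total. This is reproduced too.

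That section defines d = 0.40 as the advantage of SFP-Mind over standard SFP. In the notation above it is an assumption about M − R. The planned size and the primary analysis therefore already address the package contrast, and only the interpretive wording does not.

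**The case against.** The strongest reply is that the package comparison is already what the trial presents. The Abstract discloses the substitution openly, several sections speak of evaluating SFP-Mind as a programme, and the sample size is set for SFP-Mind over standard SFP. The design is also defensible: mindfulness on top of the full curriculum would have brought extra contact time, which matched arms avoid. The section on the experimental intervention says the original programme's structure is kept. The amount displaced may be small; the schematic overview of both interventions is in an additional file that is not shown.

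Much of this stands. The randomised comparison is valid, and the claim that an effective programme can be improved is testable for the package. The additive claim is not rescued. Within matched contact time, the Abstract says elements were dropped or changed precisely to make room. Keeping a structure is not keeping the content. A small R is possible but not shown.

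Three stronger readings are tempting, and the documents do not support them.

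- **Facilitators.** A reader might infer that the arms differ by developer delivery, since "The SFP-Mind facilitators will either be the program developers or facilitators trained by experienced personnel in teaching the novel mindfulness modules". But that sentence offers alternatives. For both programmes, "at least two of the three intervention trainers will be social workers from the field". The article does not say whether developers also run control groups. Personal mindfulness experience can fairly be seen as part of delivering the intervention. A sensitivity analysis that drops developer-led groups would not separate M from R, and the analysis plan is not shown.
- **External validity.** A reader might take the remark on real-world conditions in the Intervention fidelity section as a defence of developer delivery. In context it concerns the level of mindfulness skill asked of trainers.
- **Power.** A reader might infer that the trial is underpowered because displaced content shrinks the effect. The planned d = 0.40 is already the net difference, and any reduction would need a value for R that the article does not give.

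**Conclusion.** The point holds as a mismatch between the stated interpretation and the design. The Discussion's additive claim, and the matching wording in the Background and Study design, contradict the Abstract's description of the arms. The trial can estimate whether SFP-Mind, with mindfulness added and some SFP content removed or changed, does better than standard SFP 10–14. It cannot isolate what mindfulness adds.

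The numerical size of the gap is not estimable from the article. No stated figure is wrong, and neither the sample size nor the primary analysis is affected. The conclusion rests on one premise, taken from the Abstract, that SFP elements were in fact eliminated or changed. The additive form in the working is a simplification; any interaction between mindfulness and the retained content would only make separation harder.

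**What to change.** - In Study design and in the hypothesis at the end of the Background, state the primary question as the net effect of SFP-Mind compared with SFP 10–14, and say that SFP-Mind replaces or alters some standard elements.
- In the Discussion, delete the claim of a direct estimate of additive effects and use the same package wording for the planned conclusion.
- Add two sentences on interpretation: a null result does not show that mindfulness adds nothing, and a positive result is not attributable to mindfulness alone.
- Optionally, report facilitator type by arm as a description.

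The cost is a few sentences and a narrower claim. No data collection, sample size or model changes. The article reports the trial as ongoing, with the detailed analysis plan to be finalised before unblinding, so the wording can be settled there before results are known.

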### Trial status

The trial is ongoing. Recruitment of participants started in December 2019 and is expected to be completed in December 2020 (at the earliest). Protocol version #2; protocol version date January 8, 2020.

## Data Availability

Study material (information sheets) is available to the public and can be found at the websites http://www.familien-staerken.info and https://imac-mind.de or by request. Anonymized study data and statistical codes to analyses may be made available on request following study closure.

## Abbreviations

2D:4D: Second and fourth-finger lengths ratio
AE: Adverse events
ANCOVA: Analysis of covariance
BSI: Brief Symptom Inventory
CANTAB: Cambridge Cognition Neuropsychological Test Automated Battery
CGT: Cambridge Gambling Task
CI: Confidence interval
CONSORT: Consolidated Standards for Reporting Trials
CRO: Clinical research organization
DALY: Disability-adjusted life year
DERS: Difficulties in Emotion Regulation Scale
DRKS: Deutsches Register Klinischer Studien [German Clinical Trials Register]
DSMB: Data and Safety Monitoring Board
DVD: Digital versatile disc
EC: Emergency care
ES: Effect size
ETG: Ethyl glucuronide
GCP: Good Clinical Practice
GmbH: Gesellschaft mit beschränkter Haftung [limited liability company]
IEM-P: Interpersonal Mindfulness in Parenting scale
IMAC-Mind: Improving Mental Health and Reducing Addiction in Childhood and Adolescence through Mindfulness: Mechanisms, Prevention and Treatment
MAAS: Mindful Awareness and Attention Scale
MBCT: Mindfulness-based cognitive therapy
MBI-TAC: Mindfulness-Based Interventions—Teaching Assessment Criteria
MID: Monetary Incentive Delay
MSFP: Mindfulness-enhanced Strengthening Families Program
MSH: Medical School Hamburg
MT: Mindfulness training
PRSQ: Parental-Representation-Screening-Questionnaire
PSS-4: Perceived Stress Scale
RCT: Randomized controlled trial
SAE: Serious adverse events
SDQ: Strengths and Difficulties Questionnaire
SF-8: Short-Form Health Survey
SFP 10–14: Strengthening Families Program for Parents and Youth 10–14
SFP-Mind: Strengthening Families with Mindfulness
SST: Stop-Signal Task
SUD: Substance use disorder
SURPS: Substance Use Risk Profile Scale
THC: Tetrahydrocanabinol
TLFB: Timeline Follow-Back
